# Study Protocol. ECSSIT – Elective Caesarean Section Syntocinon^® ^Infusion Trial. A multi-centre randomised controlled trial of oxytocin (Syntocinon^®^) 5 IU bolus and placebo infusion versus oxytocin 5 IU bolus and 40 IU infusion for the control of blood loss at elective caesarean section

**DOI:** 10.1186/1471-2393-9-36

**Published:** 2009-08-24

## Abstract

**Background:**

Caesarean section is one of the most commonly performed major operations in women throughout the world. Rates are escalating, with studies from the United States of America, the United Kingdom, China and the Republic of Ireland reporting rates between 20% and 25%. Operative morbidity includes haemorrhage, anaemia, blood transfusion and in severe cases, maternal death.

The value of routine oxytocics in the third stage of vaginal birth has been well established and it has been assumed that these benefits apply to caesarean delivery as well. A slow bolus dose of oxytocin is recommended following delivery of the baby at caesarean section. Some clinicians use an additional infusion of oxytocin for a further period following the procedure. Intravenous oxytocin has a very short half-life (4–10 minutes) therefore the potential advantage of an oxytocin infusion is that it maintains uterine contractility throughout the surgical procedure and immediate postpartum period, when most primary haemorrhages occur. The few trials to date addressing the optimal approach to preventing haemorrhage at caesarean section have been under-powered to evaluate clinically important outcomes. There has been no trial to date comparing the use of an intravenous slow bolus of oxytocin versus an oxytocin bolus and infusion.

**Methods and design:**

A multi-centre randomised controlled trial is proposed. The study will take place in five large maternity units in Ireland with collaboration between academics and clinicians in the disciplines of obstetrics and anaesthetics. It will involve 2000 women undergoing elective caesarean section after 36 weeks gestation. The main outcome measure will be major haemorrhage (blood loss >1000 ml). A study involving 2000 women will have 80% power to detect a 36% relative change in the risk of major haemorrhage with two-sided 5% alpha.

**Discussion:**

It is both important and timely that we evaluate the optimal approach to the management of the third stage at elective caesarean section. Safe operative delivery is now a priority and a reality for many pregnant women. Obstetricians, obstetric anaesthetists, midwives and pregnant women need high quality evidence on which to base management approaches. The overall aim is to reduce maternal haemorrhagic morbidity and its attendant risks at elective caesarean section.

**Trial registration:**

number: ISRCTN17813715

## Background

### Systematic review of literature

Caesarean section is one of the most commonly performed major operations in women throughout the world. Rates are escalating, with studies from the developed world reporting rates between 20% and 25%. [1-3] Rates vary considerably between centres within Ireland. [4]There are many possible approaches to performing a caesarean section, the aim being to achieve safe delivery of the infant with a minimum of maternal morbidity. Operative morbidity includes haemorrhage, anaemia, blood transfusion and the risks associated with receiving donor blood products. In severe cases it may result in hysterectomy, admission to an intensive care unit or death.

The active management of the third stage at caesarean section has received little attention to date. The value of routine oxytocics in the third stage of vaginal birth has been well established [5] and it has been assumed that these benefits apply to caesarean delivery as well. [6,7] The Royal College of Obstetricians and Gynaecologists (RCOG) Guideline on caesarean section recommends a slow intravenous bolus dose of 5 IU of oxytocin following delivery of the infant. [8] This is a lower dose than used previously by many obstetric anaesthetists (10–20 IU) [9] and is based on concerns about side effects such as maternal hypotension. [10] Conversely, a conservative approach to the use of oxytocin may increase the risk of haemorrhage.

Intravenous oxytocin has a very short half-life (4–10 minutes) therefore the potential advantage of an oxytocin infusion at caesarean section is that it maintains uterine contractility throughout the surgical procedure and immediate postpartum period, when most primary haemorrhages occur. Several randomised controlled trials have compared intravenous oxytocin with oral misoprostol, 15-methyl prostaglandin F2 alpha and carbetocin, reporting little evidence of benefit with the newer agents. [6,11-13] There has been no trial to date comparing the simpler approach of an intravenous slow bolus of oxytocin versus an oxytocin bolus and infusion. Both approaches are employed within current obstetric practice but there is great variation in the approach of individual clinicians and institution. There is very limited evidence to guide practice.

A search of Medline and Embase from 1965 to 2006 and of the Cochrane Library was undertaken, for relevant systematic reviews, meta-analyses, randomised controlled trials, and other clinical trials. The date of the last search was September 2006. We intend to update this as part of a Cochrane Systematic Review, but at the time of planning and starting the trial, there were no key changes since the search of September 2006. The main keywords used were: caesarean section, blood loss, haemorrhage, oxytocin, uterotonic agent, embolic agent, randomised controlled trial. In addition, when reviewing published reference lists, key articles cited were also retrieved and reviewed. The review of the literature has been divided into use of oxytocin at varying doses and comparative use of alternative uterotonic agents.

The literature relating to the use of oxytocin bolus doses at caesarean section is presented in Table 1. The current recommendation is to use a slow bolus of 5 IU intravenously after clamping of the cord. [8] Various approaches have been tested and it is possible that smaller doses (0.3 – 5 IU) may be sufficient for elective caesarean section. [14] Nonetheless we plan to use a 5 IU bolus of oxytocin within the trial in keeping with current recommended practice. Various alternative uterotonic agents have been evaluated in randomised controlled trials. (Table 2) Most published trials to date have had between 30 and 50 participants and have been under-powered to detect important clinical outcomes such as major haemorrhage and anaemia. The largest trial of over 500 women used "need for an additional uterotonic agent" as the primary outcome measure.

**Table 1 T1:** Published studies evaluating doses of oxytocin (syntocinon)

Author, citation	Study design	Exposures	Outcome measures	Results	Conclusions
Sarna MC et al Anesth Analg 1997 84:753–6.	RCT 40 women Elective CS/regional	Oxytocin after cord clamping 5 IU vs 10 IU vs 15 IU vs 20 IU	Linear analogue of uterine tone EBL ΔHCT (pre-op/post-op)	No difference in any outcomes	No benefit in doses exceeding 5 IU
					
Zarzur Anesth Analg 1998 86:1334.	Dose-finding 20 women Elective CS	Oxytocin dosing	Uterine contractility Side effects	3 IU oxytocin Satisfactory No side effects	Low dose 3 IU sufficient
					

We propose to compare the simpler approach of oxytocin bolus versus oxytocin bolus and infusion. This will address the question whether an inexpensive and widely used drug can be employed in a more optimal way to prevent haemorrhage at caesarean section. We will be able to establish the number needed to treat to prevent one case of major haemorrhage with reasonable confidence limits.

The hypothesis is that an oxytocin infusion used in addition to an oxytocin bolus at elective caesarean section will reduce the risk of major haemorrhage and anaemia.

### National survey of current practice

Prior to undertaking this study it is important to establish current practice and the support for such a trial. A questionnaire was developed, composed of a series of closed answer questions with additional space for free text comments. The questionnaire focussed on the clinicians' use of oxytocin at caesarean section, perceived frequency of side effects, estimated average blood loss, rates of haemorrhage and willingness to participate in a future clinical trial. The questionnaire was sent to the lead consultant obstetrician and lead obstetric anaesthetist in all consultant-led obstetric units in the United Kingdom. Analysis was performed using SPSS Version 13.0 for windows. The findings of this survey are reported in detail in the European Journal of Obstetrics & Gynaecology and Reproductive Biology. [15]

Of the 434 questionnaires sent, 365 clinicians replied (response rate 84%), with none indicating that the questionnaire was inapplicable to their practice. Among the responders, 49% were lead obstetric consultants and 51% were lead obstetric anaesthetists. The various approaches to the use of oxytocin at the time of caesarean section are presented in Table 3. A slow bolus of 5 IU oxytocin was the preferred approach of obstetricians and anaesthetists (153, 86% and 171, 92% respectively). Routine oxytocin infusions were used by 72 clinicians (20%), and selective infusions were used for particular clinical situations by 289 (80%). Most clinicians used either 30 IU (158, 43%) or 40 IU (192, 53%) infusions over 4 hours, with a total of 38 different regimens. The perceived risk of side effects with oxytocin was low, particularly for infusions. Estimated "average" blood loss varied (150–1500 ml) with 56 clinicians (17%) and 93 (28%) reporting a >20% risk of postpartum haemorrhage for elective and emergency caesarean sections, respectively.

**Table 3 T3:** Percentages refer to complete responses

	All n = 365 (%)	Obstetricians n = 179 (%)	Anaesthetists n = 186 (%)
Slow bolus 5 IU oxytocin	324 (89.5)	153 (86.4)	171 (92.4)
Slow bolus 10 IU oxytocin	44 (12.1)	28 (15.6)	16 (8.6)
Additional 5 IU bolus if clinically indicated	61 (17.0)	17 (9.5)	44 (23.5)
Routine use of oxytocin infusion	72 (19.8)	33 (18.4)	39 (21.1)
Selective use of oxytocin infusion	289 (79.8)	145 (81.0)	144 (78.7)
30 IU oxytocin infusion	158 (43.3)	83 (46.4)	76 (40.9)
40 IU oxytocin infusion	192 (53.3)	90 (50.8)	102 (55.0)

Approaches to the use of oxytocin at the time of caesarean section

This national survey of practice in the use of oxytocin for the prevention of blood loss at caesarean section found general consistency in the use of bolus oxytocin but a great deal of variation in the use of additional oxytocin infusions. The perceived risk of side effects with oxytocin was low, particularly for infusions. Obstetricians and anaesthetists reported a high rate of excess haemorrhage at caesarean section and more than half of the clinicians surveyed would participate in a randomised controlled trial comparing oxytocin bolus with bolus and infusion. There is wide variation in the approach to prevention of haemorrhage at caesarean section, reflecting a lack of robust evidence. This survey supports the need for further research into this important aspect of intrapartum care. The preferred approach was to use a 40 IU infusion of oxytocin in a solution of 0.9% saline in keeping with the recommendations of the Advanced Life Support in Obstetrics (ALSO) courses. This is the regimen we plan to use for the proposed trial.

The survey was carried out within the UK as the original plan (prior to relocation of the PI) was to conduct the study in Scotland. The practice of clinicians in Ireland is very similar to reported practice in the UK.

The hypothesis is that an oxytocin infusion used in addition to an oxytocin bolus at elective caesarean section will reduce the risk of major haemorrhage and anaemia.

### Aims and objectives

The aim of this study is to compare the effects of an intravenous slow bolus of oxytocin (5 IU) and placebo infusion (500 ml 0.9% saline) with an intravenous slow bolus of oxytocin (5 IU) and oxytocin infusion (40 IU in 500 ml 0.9% saline over 4 hours) at elective caesarean section in a double blind randomised trial.

Specific objectives are as follows:

### Primary outcomes

- to compare the incidence of major obstetric haemorrhage (≥ 1000 ml) following oxytocin bolus compared with oxytocin bolus and infusion

- to compare the need for an additional uterotonic agent between the two groups

Major obstetric haemorrhage will be defined by:

- measured blood loss as calculated from pre and post-operative haematocrit (see below)

### Secondary outcomes

- to compare the estimated mean operative blood loss between the two groups (as measured by theatre staff)

- to compare early lochial loss following oxytocin bolus compared with oxytocin bolus and infusion

- to compare the objective change in haemoglobin and haematocrit before and 48 hours after delivery between the two groups

- to compare the incidence of severe anaemia (Hb fall ≥ 20%) 48 hours after delivery between the two groups (or patient transfused).

- to compare the need for blood transfusion and/or blood products

- to compare the incidence of side effects (vomiting, hypotension)

- to compare the postnatal length of stay in theatre/recovery and in the hospital

### Cost-effectiveness

- to compare the cost-effectiveness of an oxytocin bolus regimen versus oxytocin bolus and infusion (separate protocol).

## Methods and design

### Recruitment and allocation

#### Inclusion criteria

The study will be limited to healthy women at term (> 36 weeks) with singleton pregnancies who are booked for elective caesarean section.

#### Exclusion criteria

Women with placenta praevia, thrombocytopenia, coagulopathies, a previous major obstetric haemorrhage (≥ 1000 ml), known fibroids or receiving anti-coagulant therapy will be excluded as will women who do not understand English and women under the age of 18 years. Other patients may be excluded at the clinician's discretion if a major haemorrhage is anticipated.

Women will be recruited to the trial in the third trimester when initial arrangements are being made for a booked elective caesarean section. The antenatal clinic midwife or research midwife/fellow will approach eligible women and offer information about the study. Women return on the day of surgery and spend a number of hours on the day ward or antenatal ward prior to surgery. At that point the woman's interest in participation in the study will be confirmed, an opportunity to ask additional questions will be provided and informed written consent will be completed. Randomisation will be performed using an automated web-based randomisation system hosted by the Bristol Randomised Trials Collaboration, a UKCRN-registered trials unit. Allocation will be stratified by centre and previous caesarean section (no/yes), and blocked using random permuted blocks of varying size.

The active or placebo infusion will be prepared by the research fellow/midwife. This will be done in the pharmacy department, away from theatre and will be labelled as "Trial drug – Placebo or 40 IU oxytocin". This will ensure blinding of everyone except the research fellow who makes up the infusion, and they will have no role in the management of the patient. Having the research fellow blinded is not possible for two reasons. Firstly, it is not possible to pre-prepare the infusions due to a lack of knowledge of the stability of oxytocin. Secondly, it has not been possible to obtain identically matched placebo ampoules.

### Intervention

Following written informed consent women will be randomised to receive either an intravenous slow bolus of oxytocin 5 IU and a placebo infusion (0.9% saline solution 500 ml over 4 hours), or oxytocin bolus 5 IU and oxytocin infusion (40 units in 500 ml 0.9% saline over 4 hours). Both the patient and the health care staff will be blinded to the intervention. The hospital pharmacist will produce numbered treatment kits containing either 1 × 5 IU ampoule or 1 × 5 IU ampoule and 4 × 10 IU ampoules. There will be labels and instructions for the research fellow to prepare the infusion so that the anaesthetist and other members of the investigator team remain blinded to the randomised treatment.

It is important that the surgical approach to caesarean section is standardised. Surgeons will be asked to operate to a standard procedure that specifies controlled cord traction for delivery of the placenta after administration of the oxytocin bolus, two layer closure of the uterine incision, and to avoid delivering the uterus for suturing unless clinically indicated. Deviations from the standard procedure will be recorded. Should the uterus remain atonic despite the trial intervention, the obstetrician/anaesthetist can use an additional uterotonic agent either replacing the trial infusion with a known infusion of oxytocin and/or use of a further agent.

Measurement of operative blood loss will be standardised. Disposable waterproof drapes are in use with pockets that capture all body fluids. The suction volume is measured. All swabs are weighed to measure additional blood loss. A more objective measure of blood loss will be calculated using pre- and post-operative haematocrit (see outcome measures below).

Anaesthesia will also be standardised. An intravenous bolus of 500 ml crystalloid should be given to all patients prior to spinal anaesthesia. A size 25G pencil-point needle should be used at a suitable lumbar interspace. The patient can be sitting or in the left lateral position for spinal anaesthesia. The anaesthetic solution will consist of 2 ml 0.5% hypertonic bupivocaine (2.2 ml in the sitting position), 10–20 μg fentanyl and 0.1 mg preservative free morphine. Anaesthesia should be to the level of T5, as assessed by touch. The patient will be tilted 15° to the left of supine and standard monitoring used as per the AAGBI guidelines. The sphygmomanometer cuff should be placed on the left arm. Haemodynamic monitoring will be performed before spinal anaesthesia, every minute until 10 minutes after delivery, every 15 minutes during the first postoperative hour then every 30 minutes for 4 hours. For the purpose of this study, baseline haemodynamic variables will be regarded as those immediately after clamping of the cord and before administration of syntocinon 5 IU. The investigators accept that individual anaesthetists may deviate from this protocol according to clinical needs. This is acceptable and should be documented on the case report form.

Intraoperative hypotension will be treated with intravenous boluses of phenylephrine 50 μg. If the heart rate falls below 60/min, intravenous boluses ephedrine 6 mg will be substituted. The anaesthetist will aim to maintain blood pressure at preoperative values. After delivery, the operating table tilt will be removed and the patient placed in the full supine position. Blood loss at operation will be replaced with colloid infusion or blood as deemed necessary by the anaesthetist. Postoperative pain relief will consist of regular non-steroidal analgesia combined with paracetamol. Opiates in the form of oxynorm can be used with caution considering the use of intrathecal opiates. Again it is acceptable for the local administrator to use any form of analgesia as per local practice and to document it on the case report form.

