### Data monitoring and Ethics Committee (DMEC)

An independent safety and data monitoring committee will also be formed. They will meet yearly to examine recruitment figures, baseline data, retention and adverse events. The DMEC will not undertake any formal interim analyses for either safety or effectiveness and therefore there are no formal stopping rules. There is no evidence of adverse reactions associated with oxytocin infusion. Although adverse reactions have been shown to be associated with the 5 IU oxytocin bolus, all trial participants will receive a bolus, and thus we do not anticipate any differences in rates of adverse events between the groups. However all adverse events will be reported to the DMEC who will report these data to the Trial Steering Committee. Additionally, in the event of a postpartum haemorrhage, clinicians are permitted to discontinue the trial infusion and commence a known 40 IU oxytocin infusion.

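### The haemodynamic schedule lists no study reading from 10 minutes after delivery to the end of surgery, and hypotension is counted with no time window; both tend to dilute the arm comparison for this secondary safety outcome

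*Protocol article*

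**What the plan says.** All references are to the protocol article.

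- **Reading schedule (Intervention).** After a reading before the spinal, monitoring is "every minute until 10 minutes after delivery, every 15 minutes during the first postoperative hour then every 30 minutes for 4 hours". The same paragraph calls for "standard monitoring used as per the AAGBI guidelines", without giving a recording interval.
- **Study baseline (Intervention).** "baseline haemodynamic variables will be regarded as those immediately after clamping of the cord and before administration of syntocinon 5 IU".
- **Treatments (Intervention).** One arm receives "an intravenous slow bolus of oxytocin 5 IU and a placebo infusion (0.9% saline solution 500 ml over 4 hours"); the other receives the same bolus and "oxytocin infusion (40 units in 500 ml 0.9% saline over 4 hours"). No infusion start time relative to delivery or bolus is given.
- **Pressors (Intervention).** Phenylephrine is the first treatment for intraoperative hypotension; ephedrine replaces it when the heart rate drops under 60 per minute.
- **Outcome (Secondary outcomes; Outcome measures).** One objective is "to compare the incidence of side effects (vomiting, hypotension"). Hypotension means a pressure more than 30% lower than the pre-operative value, or ephedrine given, or both. No period is attached to the definition.
- **Expectation (Data monitoring and Ethics Committee).** "all trial participants will receive a bolus, and thus we do not anticipate any differences in rates of adverse events between the groups".
- **Pharmacology (Systematic review of literature).** "Intravenous oxytocin has a very short half-life (4–10 minutes").

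**The concern.** The trial randomises only the infusion. The spinal and the bolus are common to both arms, and that is where the minute-by-minute readings fall. The schedule then passes to the first postoperative hour without listing anything for the rest of the operation, although the protocol's own rationale is that the infusion acts during surgery as well as after it.

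Two features then work in the same direction. First, the outcome has no start point and refers to pre-operative pressure, so a woman who becomes hypotensive after the spinal is already an event before her allocation can matter. Second, a fall in the unlisted interval that is treated with phenylephrine becomes an event only if a qualifying pressure is written down.

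Both tend to pull the arms together on hypotension, one of the two side effects that the protocol names. Because the protocol already expects no difference in adverse events, a diluted null could be read as confirming that expectation.

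**Working it through.** The protocol states no power or expected rate for hypotension, so there is no figure to reproduce.

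**1. The two sections side by side**

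| Item | Intervention | Outcome measures |
|---|---|---|
| Reference pressure | After cord clamping, before the bolus | Pre-operative |
| Period covered | Listed to 10 minutes after delivery, then from the postoperative period | None stated |
| Pressor | Phenylephrine first, ephedrine if heart rate is low | Only ephedrine counts |

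The article does not say which analysis uses the post-clamp baseline.

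**2. Exposure around the interval**

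Inputs: 5 IU bolus in both arms, 40 IU over 240 minutes in one arm, half-life 4–10 minutes. Assumptions: one compartment, and bolus at delivery (t = 0).

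- Infusion rate R = 40/240 = 0.167 IU/min. If started with the bolus, 1.67 IU (4.2% of 40 IU) has been given by 10 minutes.
- Bolus remaining = 5·exp(−kt).
- Infusion in the body = (R/k)·(1 − exp(−k(t − start))).
- k = ln 2 / half-life. The plateau R/k is 0.96 IU (half-life 4) to 2.40 IU (half-life 10).

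Worked case, half-life 10, start 0, t = 10: bolus 2.50 IU, infusion 1.20 IU, ratio 3.70/2.50 = 1.48.

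Ratio of active to placebo amount in the body (range over half-lives 10 and 4):

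| Infusion start | 5 min | 10 min | 20 min |
|---|---|---|---|
| 0 min | 1.20–1.27 | 1.48–1.90 | 2.4–7.0 |
| 5 min | 1.00 | 1.28–1.63 | 2.2–6.7 |
| 10 min | 1.00 | 1.00 | 2.0–6.1 |

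Whichever start time applies, the ratio is larger at 20 minutes than at any point in the dense window. Later ratios grow very large only because the bolus has almost gone; the infusion's absolute amount stays below the 5 IU bolus.

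**3. Length of the interval**

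Assume surgery ends 20–60 minutes after delivery (not stated in the protocol).

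- Interval = 20 − 10 = 10 minutes, up to 60 − 10 = 50 minutes.
- Share of the infusion = 10/240 = 4% to 50/240 = 21%.
- If the infusion starts at delivery, 240 − 60 = 180 to 240 − 20 = 220 minutes of it remain, under about 4 + 8 = 12 scheduled postoperative readings.

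**4. Dilution from events before the infusion (illustration; all rates assumed)**

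Let q be the proportion in each arm already counted before the infusion, and r the true risk afterwards, independent of q. Then P(ever hypotensive) = q + (1 − q)r, and the arm difference is (1 − q)(r₁ − r₀). Take r₀ = 5% and r₁ = 10% with 1000 per arm. Power = Φ(difference/SE − 1.96).

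| q | Rates | Difference | SE | Power |
|---|---|---|---|---|
| 0 | 5% v 10% | 5 points | 0.0117 | 99% |
| 20% | 24% v 28% | 4 points | 0.0196 | 53% |
| 60% | 62% v 64% | 2 points | 0.0216 | 15% |

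If a share m of post-start events also goes unrecorded in both arms, the difference becomes (1 − q)(1 − m)(r₁ − r₀). The documents give no value for m.

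**The case against.** The strongest reply has four parts.

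- **Women are monitored throughout.** Guideline monitoring applies during surgery, and hypotension is to be treated. The outcome is not limited to scheduled readings, and ephedrine given in the interval counts. This stands: the interval is unlisted for the study, not unmonitored. It does not settle the point, because the first-line pressor does not count and no study recording is specified for those readings.
- **Detail may sit elsewhere.** The full protocol or case report form may define intraoperative recording, and an article may leave that to them. This is fair in part. But the article prints what reads as a complete schedule and fixes an outcome definition whose baseline differs from the one beside the schedule.
- **The scale is modest.** Most of the 4-hour infusion falls under scheduled postoperative readings. This stands.
- **The protocol expects no harm from the infusion.** It says there is no evidence of adverse reactions to it. That is a prior view; the comparison of side effects is there to test it.

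A reader might go further and infer that the arms are practically identical during the minute-by-minute readings, or that infusion-related hypotension would first appear in the unlisted interval. The documents support neither. The infusion start time is not given; if it starts with the bolus, the infusion is at 50–82% of plateau by 10 minutes and exposure may already differ 1.5–1.9-fold. No section says when infusion-related hypotension would occur.

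**Conclusion.** The point holds as a weakness in how one secondary safety outcome is captured and counted. Followed as written, the plan counts hypotension that precedes any randomised difference, and it lists no study reading for the rest of the operation while exposure is separating. Both features tend to shrink a true arm difference.

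Counting pre-infusion events could be the larger effect: under the assumed rates a 5-point difference falls to 4–2 points and power from about 99% to about 53–15%. The unlisted interval adds an amount that cannot be estimated from the document; it covers about 4–21% of the infusion if surgery ends 20–60 minutes after delivery. These sizes rest on assumed event rates, independence between periods, an assumed operating time and a one-compartment model. Primary outcomes and sample size are untouched.

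**What to change.** 1. Reconcile the Intervention and Outcome measures sections on what is recorded for the study between 10 minutes after delivery and the end of surgery, which baseline the hypotension outcome uses, and from when events are counted.
2. Transcribe to the case report form the intraoperative readings already taken under standard monitoring, through to the end of surgery.
3. Record the time at which the trial infusion starts.
4. Report hypotension separately before and after infusion start, so that the randomised comparison can be read apart from events caused by the spinal.

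The cost is extra transcription from the anaesthetic chart and one case report form page. This changes data capture and reporting only; no treatment or clinical monitoring rule changes.
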